## Methods/design

### Aims of the trial

This study aims to compare the effectiveness of a web-based self-help intervention alone or combined with chat counseling in the reduction of the cannabis use of problematic cannabis users via a three-arm randomized controlled trial. The primary outcome is the weekly quantity of cannabis consumed (measured in the number of standard joints per week) at the 3-month follow up. The secondary outcome measures include the frequency of cannabis use days (7 day point prevalence of cannabis use days), changes in problematic cannabis use, severity of cannabis dependence, cannabis withdrawal symptoms, cannabis craving, the use of other psychoactive substances, mental health symptoms, functional health states, intervention satisfaction, and treatment retention. The predictive validity of participant characteristics for treatment retention and primary and secondary outcomes will be explored.

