### Hypotheses

We hypothesize that web-based interventions, which are more interactive, will be more effective in reducing cannabis use among problematic cannabis users. We will test the following detailed study hypotheses with respect to the main outcome, i.e., reduction of the quantity of cannabis used between the baseline and the 3-month follow up:

1. Tailored chat-based counseling in combination with web-based self-help for the reduction of cannabis use (study arm 1) is more effective than the waiting list control condition (study arm 3).

2. Web-based self-help for the reduction of cannabis use (study arm 2) is more effective than the waiting list control condition (study arm 3).

3. Chat-based counseling in addition to web-based self-help for the reduction of cannabis use (study arm 1) is by trend more effective than web-based self-help alone (study arm 2).

Moreover, we expect the participants of study arm 1 to improve more than those in study arm 2 with respect to the secondary outcomes between the baseline and the three-month follow up termination.

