### Measurement instruments

The primary outcome measures of cannabis consumption will be recorded as the 7-day point prevalence of the quantity of cannabis used, quantified in pre-defined standard cannabis joint sizes, as specified in the consumption diary (see also Table 
1). In the first step, participants will choose between three different cannabis forms presented in photographs (low potency cannabis plant, high potency cannabis plant, or cannabis resin). In the second step, five different standard joints for every category will be presented (1/10 g, 1/6 g, 1/4 g, 1/3 g, 1/2 g; pictures will come from the global drug survey cannabis meter
[32]); these joints will either be pure cannabis or cannabis mixed with tobacco. A standard tobacco cigarette, a ruler with centimeter and millimeter scales, the fraction amount in grams, and an open 10 cm paper prepared to roll a joint and containing the cannabis plant/resin-tobacco mixture or pure cannabis will be presented. Participants will choose which picture most closely approximates the cannabis joints they most often smoke. Those who smoke cannabis in different preparations (e.g., in a bong, a vaporizer, etc.) will choose the photograph that most closely approximates the amount of cannabis their usually consume. The final chosen picture will be placed in the individual consumption diary, and participants will be asked to convert the quantities of the cannabis they smoke into units relative to that picture if they consume cannabis for once in forms other than their common standard joint (rule of thumb that one high potency joint is equal to two low potency cannabis joints of identical content weight, one cannabis resin joint is equal to three low potency joints of identical content weight, etc.; identical content weight pictures will be presented on a separate page). Participants will also have the opportunity to indicate quantities below one common standard joint down to one tenth of a joint (they will also be able to indicate quarter-joint). Quantities smaller than one joint are expected for those who share cannabis joints with others.

**Table 1 T1:** Measurements and instruments

**Assessments/instruments**	**Baseline**	**1 week**	**3 weeks**	**6 weeks**	**3-month follow up**
Socio-demographics	x				
MHI-5	x				x
CLAMES^1)^	x				x
Quantity of Cannabis use^2)^	x	x	x	x	x
Frequency of Cannabis use^2)^	x	x	x	x	x
CUDIT	x				x
SDS	x			x	x
CWS		x	x		
CCS-7		x	x		
FDA	x			x	x
Intervention Satisfaction				x	

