^1)^ Additional retrospective cost-relevant information directly or indirectly related to cannabis use will be collected by the CLAMES to conduct cost-effectiveness and cost-utility analyses.

^2)^ 7-day point prevalences of the quantity (in common standard joints) and frequency (the number of days on which cannabis is used) of cannabis use will be derived from the consumption diary assessed daily using data from the last 7 days.

Moreover, the following secondary outcome instruments will be applied: 1) cannabis consumption days per week according to the consumption diary; 2) the Cannabis Use Disorders Identification Test (CUDIT), which is a 10-item questionnaire
[33] that was constructed by adapting the Alcohol Use Disorders Identification Test (AUDIT
[34]). To cover the length of the trial length, this instrument will be adapted to focus on the last 3 months in its planned assessments (baseline and 3-month follow up); 3) The Severity of Dependence Scale (SDS), which is a 5-item questionnaire that measures the severity of cannabis dependence. Each of the five items is scored on a 4-point scale (0–3). The total score is obtained through the addition of the ratings on all 5 items. High scores indicate high levels of dependency
[35]; 4) The Cannabis Withdrawal Scale (CWS)
[36], which is a 26-item questionnaire containing statements that describe cannabis withdrawal symptoms within the last 24 hours on 11-point scales (0–10); 5) The Cannabis Craving Symptoms questionnaire (CCS-7), which is a 7-item questionnaire
[37] derived from the Marijuana Craving Questionnaire
[38]. Each item is rated on a 7-point-scale (1–7); 6) the “Fragebogen Substanzanamnese” (FDA), which is a questionnaire that ascertains the number of years of consumption over the lifetime, the past month’s consumption, and the manner of consumption for DSM-IV/ICD-10 substances of abuse. This measure was derived from the Europe ASI
[39]; 7) the short version of the Mental Health Inventory (MHI-5)

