### Handling of study dropouts

Each week, participants in intervention arms one and two will be sent an automated e-mail that will contain a reminder to login to their consumption diary, a reminder to work on their modules and a direct link to the Can Reduce login site. If participants do not log in, they will receive a reminder e-mail every three days for the following two weeks. If they do not continue their participation after these reminders, they will be considered to have dropped out of the study. Participants allocated to study arm 1 (chat and self-help) will additionally be invited to the first chat session at least three times over two weeks if they do not respond. In each of these invitations they will be asked to agree to attend two chat sessions on dates suggested by their counselor. If the participants are unable to attend on these dates, they will have the opportunity to suggestion dates to the counselor. This procedure will be repeated until a first chat date has been found. If participants do not show up at the agreed chat date they will be sent new chat dates until a first chat appointment occurs. If participants do not reply after three invitations to schedule chat appointment, they will be considered to have dropped out of the study. The second chat appointment will be scheduled at the end of the first chat session. If participants do not show up for the second session, they will be sent new chat dates twice. Attendance of at least one chat appointment will be required of the participants, otherwise they will be considered to have dropped out. Participants in study arm 1 who discontinue their consumption dairies but proceed with the chat session will not be considered as drop outs and will be included in the study.

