### Data analysis

Data will be analyzed according to the intention-to-treat principle (ITT). For the ITT analyses, we will apply the multiple imputations procedure (MICE) of STATA, which imputes missing data using all available baseline variables (sociodemographic and health- and cannabis-related variables). Baseline measurements will be compared using t- and Chi-squared tests. Differences between primary and secondary outcome variables between baseline and the follow up points will be tested using generalized estimating equation (GEE) models. GEE is a repeated-measures regression model that takes into account the correlations between the repeated measures from each person
[45]. We will perform logistic GEE analyses for the binary outcome variables and linear GEE analysis for continuous outcome variables. Results from the imputed data set will be cross-checked with the non-imputed data set.

We will conduct additional exploratory regression analyses to determine whether baseline variables predict the severity of cannabis use disorder (CUDIT, SDS), cannabis craving (CCS-7), cannabis withdrawal (CWS), reduced psychiatric symptoms (MHI-5), and treatment retention. For these analyses, we will use linear, multinomial, or binary regression models depending on the scale of the outcome measure.

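### Withdrawal (CWS) and craving (CCS-7) are scheduled only at weeks 1 and 3, so the stated comparison from baseline to 3 months cannot be carried out for these two secondary outcomes

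*Protocol article*

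**What the plan says.** All references are to the protocol article.

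- **Aims of the trial.** Both constructs are in the list of secondary outcomes, which includes "severity of cannabis dependence, cannabis withdrawal symptoms, cannabis craving, the use of other psychoactive substances". The Measurement instruments section numbers the CWS and the CCS-7 as the fourth and fifth secondary instruments.
- **Hypotheses.** Arm 1 is expected to improve more than arm 2 "with respect to the secondary outcomes between the baseline and the three-month follow up termination". No secondary outcome is exempted.
- **Data analysis.** "Differences between primary and secondary outcome variables between baseline and the follow up points will be tested using generalized estimating equation (GEE) models". Again there is no exemption.
- **Table 1 ("Measurements and instruments").** The CWS and CCS-7 rows are marked in the 1-week and 3-week columns only. The baseline, 6-week and 3-month cells are empty. No other section adds an assessment of either scale.

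**The concern.** The article fixes both the assessment schedule and the comparison, and for two named secondary outcomes they do not fit together. A change from baseline needs a baseline score, and a 3-month result needs a 3-month score. Neither is scheduled for withdrawal or craving.

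An analysis plan written later could redefine the comparison, but it could not create a measurement that was never taken. If the schedule is followed as printed, the trial will have no change from the pre-treatment state and no 3-month result for these two outcomes. The analysts would then have to choose a replacement comparison after the fact, for outcomes on which a direction of effect has been stated in advance.

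**Working it through.** No power or sample-size figure enters this point. The check sets the schedule against the stated comparison.

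**Step 1: is the table read correctly?** The CUDIT row is marked at baseline and 3 months. The text independently says the CUDIT is adapted to cover three months "in its planned assessments (baseline and 3-month follow up"). Row and text agree, so the column alignment can be trusted.

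**Step 2: which secondary instruments support a comparison from baseline to 3 months?**

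| Numbered instrument | Baseline | 3 months | Other times |
|---|---|---|---|
| Days of use per week | yes | yes | weeks 1, 3, 6 |
| CUDIT | yes | yes | none |
| SDS | yes | yes | week 6 |
| CWS | no | no | weeks 1, 3 |
| CCS-7 | no | no | weeks 1, 3 |
| FDA | yes | yes | week 6 |
| MHI-5 | yes | yes | none |
| CLAMES | yes | yes | none |

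Six of eight have both required time points. The CWS and the CCS-7 each have 0 of 2. Satisfaction and retention also lack a baseline, but by their nature, so they do not raise the same conflict.

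**Step 3: which statement conflicts with which gap?** The Data analysis text measures differences from baseline but refers only to follow-up points, without naming 3 months. The missing baseline therefore conflicts with both the Data analysis and the Hypotheses sections. The missing 3-month score conflicts with the Hypotheses section alone.

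**Step 4: can imputation fill the gap?** The procedure "imputes missing data using all available baseline variables (sociodemographic and health- and cannabis-related variables"). An imputation model for a score needs some participants in whom that score was observed. At baseline and at 3 months, 0 of the planned 267 participants would have a CWS or CCS-7 score, so there is nothing to fit the model to.

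**Step 5: can week 1 stand in for baseline?** No. The Trial flow section opens all modules from the first day, and the Discussion recommends cutting use by 20 to 30 percent or more in the first week. The CWS asks only about the preceding 24 hours, so a week-1 score does not describe the pre-treatment state. If d1 and d3 are the between-arm differences at weeks 1 and 3, the between-arm difference in change from week 1 to week 3 is d3 − d1. Any effect already present at week 1 is subtracted out.

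**Step 6: what remains?** Randomisation makes d1 and d3 valid between-arm contrasts without a baseline score. What is missing is the precision from adjusting for that score: with correlation r between baseline and outcome, adjustment multiplies the residual variance by about 1 − r². The documents give no r, so the loss is not quantified here. Baseline SDS, CUDIT and quantity of use can recover part of it.

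**The case against.** The strongest defence is that the timing is sensible and only the wording is loose. Participants are advised to reduce early, and withdrawal is asked about over 24 hours, so measuring it in the first weeks is coherent; a CWS score before any reduction, or at 3 months, is not clearly more informative. The sentence on secondary outcomes is also phrased as an expectation, while the explicit commitment to test hypotheses concerns the main outcome.

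Part of this stands. Early measurement of withdrawal may be deliberate, and the fix allows for that. But the article gives no such rationale, the argument is weaker for craving, and the Data analysis section separately commits to testing secondary outcomes from baseline.

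A reader might infer three stronger points that the document does not support:

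- **The predictor models also fail.** They do not. Those regressions use baseline variables as predictors and the two scales as outcomes, with no time point fixed. Week-1 or week-3 scores are enough.
- **The week-1 and week-3 data are unusable without a baseline.** They are not, for the reason in the last step of the working.
- **Weeks 1 and 3 come before the chat sessions.** The Handling of study dropouts section says arm 1 participants "will additionally be invited to the first chat session at least three times over two weeks", but the sentence goes on to limit this to people who do not respond. It does not describe the usual participant.

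**Conclusion.** The point holds as an internal contradiction, not as a missing detail. For two of the eight numbered secondary instruments, the change from baseline cannot be calculated and there is no 3-month result. The precision from adjusting for the same scale at baseline is also lost. The randomised comparison at weeks 1 and 3 and the exploratory regressions survive. The primary outcome, the sample size and the three numbered hypotheses are untouched, so this should be corrected but does not threaten the main result.

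The conclusion rests on Table 1 being the complete schedule for these scales, which nothing else in the article contradicts. Table 1 does not separate the arms. The surviving comparison assumes that both intervention arms complete the scales at weeks 1 and 3; whether the waiting-list arm does so is not stated.

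**What to change.** Reconcile Table 1 with the Hypotheses and Data analysis sections.

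1. Add at least the CCS-7 to the baseline and 3-month online assessments in all arms. The planned GEE comparison can then be run for craving.
2. Either do the same for the CWS or take it out of the comparison from baseline to 3 months. For any scale not added, define the analysis as a between-arm comparison at weeks 1 and 3, adjusted for baseline variables already collected, such as SDS, CUDIT and quantity of use. State which arms are compared.

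**Cost.** The CCS-7 alone adds 7 items at each of two existing assessments, 7 × 2 = 14 responses per participant. Both scales add 26 + 7 = 33 items, or 33 × 2 = 66 responses. The baseline already takes about 20 minutes and the article expects high attrition, so the extra burden of the full CWS is a fair reason to choose the wording route for that scale. That route costs only a sentence in each section. The items must be added before enrolment to be complete: for anyone already enrolled without a baseline score, only the restated comparison is available.

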### Measurement instruments

The primary outcome measures of cannabis consumption will be recorded as the 7-day point prevalence of the quantity of cannabis used, quantified in pre-defined standard cannabis joint sizes, as specified in the consumption diary (see also Table 
1). In the first step, participants will choose between three different cannabis forms presented in photographs (low potency cannabis plant, high potency cannabis plant, or cannabis resin). In the second step, five different standard joints for every category will be presented (1/10 g, 1/6 g, 1/4 g, 1/3 g, 1/2 g; pictures will come from the global drug survey cannabis meter
[32]); these joints will either be pure cannabis or cannabis mixed with tobacco. A standard tobacco cigarette, a ruler with centimeter and millimeter scales, the fraction amount in grams, and an open 10 cm paper prepared to roll a joint and containing the cannabis plant/resin-tobacco mixture or pure cannabis will be presented. Participants will choose which picture most closely approximates the cannabis joints they most often smoke. Those who smoke cannabis in different preparations (e.g., in a bong, a vaporizer, etc.) will choose the photograph that most closely approximates the amount of cannabis their usually consume. The final chosen picture will be placed in the individual consumption diary, and participants will be asked to convert the quantities of the cannabis they smoke into units relative to that picture if they consume cannabis for once in forms other than their common standard joint (rule of thumb that one high potency joint is equal to two low potency cannabis joints of identical content weight, one cannabis resin joint is equal to three low potency joints of identical content weight, etc.; identical content weight pictures will be presented on a separate page). Participants will also have the opportunity to indicate quantities below one common standard joint down to one tenth of a joint (they will also be able to indicate quarter-joint). Quantities smaller than one joint are expected for those who share cannabis joints with others.

**Table 1 T1:** Measurements and instruments

**Assessments/instruments**	**Baseline**	**1 week**	**3 weeks**	**6 weeks**	**3-month follow up**
Socio-demographics	x				
MHI-5	x				x
CLAMES^1)^	x				x
Quantity of Cannabis use^2)^	x	x	x	x	x
Frequency of Cannabis use^2)^	x	x	x	x	x
CUDIT	x				x
SDS	x			x	x
CWS		x	x		
CCS-7		x	x		
FDA	x			x	x
Intervention Satisfaction				x	

^1)^ Additional retrospective cost-relevant information directly or indirectly related to cannabis use will be collected by the CLAMES to conduct cost-effectiveness and cost-utility analyses.

^2)^ 7-day point prevalences of the quantity (in common standard joints) and frequency (the number of days on which cannabis is used) of cannabis use will be derived from the consumption diary assessed daily using data from the last 7 days.

Moreover, the following secondary outcome instruments will be applied: 1) cannabis consumption days per week according to the consumption diary; 2) the Cannabis Use Disorders Identification Test (CUDIT), which is a 10-item questionnaire
[33] that was constructed by adapting the Alcohol Use Disorders Identification Test (AUDIT
[34]). To cover the length of the trial length, this instrument will be adapted to focus on the last 3 months in its planned assessments (baseline and 3-month follow up); 3) The Severity of Dependence Scale (SDS), which is a 5-item questionnaire that measures the severity of cannabis dependence. Each of the five items is scored on a 4-point scale (0–3). The total score is obtained through the addition of the ratings on all 5 items. High scores indicate high levels of dependency
[35]; 4) The Cannabis Withdrawal Scale (CWS)
[36], which is a 26-item questionnaire containing statements that describe cannabis withdrawal symptoms within the last 24 hours on 11-point scales (0–10); 5) The Cannabis Craving Symptoms questionnaire (CCS-7), which is a 7-item questionnaire
[37] derived from the Marijuana Craving Questionnaire
[38]. Each item is rated on a 7-point-scale (1–7); 6) the “Fragebogen Substanzanamnese” (FDA), which is a questionnaire that ascertains the number of years of consumption over the lifetime, the past month’s consumption, and the manner of consumption for DSM-IV/ICD-10 substances of abuse. This measure was derived from the Europe ASI
[39]; 7) the short version of the Mental Health Inventory (MHI-5)
[40], which is a validated and user-friendly self-assessment questionnaire that assesses recent mental distress and self-reported diagnoses of depression; 8) the CLAMES, which is a standardized measure of functional health states that provides a simple, generic measure of health for clinical and economic appraisal. This instrument consists of a descriptive system to measure pain/discomfort, physical functioning, emotional state, fatigue, memory and thinking, social relationships, anxiety, speech, hearing, vision, and use of hands and fingers on four or five levels that range from no problems to extreme problems
[41]. Overall intervention satisfaction will be ascertained on a visual analogue scale from absolutely unsatisfied to absolutely satisfied. Finally, retention will be derived from the last cannabis use input entered into the consumption diary in study arms one and two.

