**Figure 1 F1:**
[figure not shown]
**Trial flowchart.** This figure provides an overview of the participant flow for this trial.

Study arm one and two involve weekly reminder e-mails to login and fill out a consumption diary. The following modules, organized into three main parts, are offered as a web-based self-help intervention (study arms one and two):

• Part 1: Introduction

• Registration process

• Explanation of the cannabis consumption diary and its fully automated progress charts and statistics

• Examination of the pros and cons resulting from a change in cannabis consumption patterns and further principles of motivational interviewing to address motivation

• Explanation of the “My Can Reduce” folder (this folder allows individuals to review the acquired summarized module documents, e.g., the list of the top five strategies for dealing with cannabis cravings)

• Explanation of the emergency button for immediate responses to frequently asked questions and access to emergency contacts

• Part 2: Key Modules (participants are encouraged to complete these modules in the order presented below)

• Module 1: Strategies for goal achievement

• Module 2: Identifying risk situations

• Module 3: Dealing with cannabis craving

• Module 4: Dealing with relapses

• Part 3: Further Modules (participants are encouraged to complete at least two, in any order)

• Module 5: Tobacco smoking during the reduction of cannabis use

• Module 6: Saying “no” to foster refusal skills

• Module 7: Dealing with burdens

• Module 8: Preserving achievements

Furthermore, a glossary that explains the terms, definitions, and concepts used in the intervention, information about the history of cannabis use, the short-, medium- and long-term effects of cannabis, the physical risks of cannabis (COPD, lung cancer, cardio-vascular, etc.), co-occurring mental health problems (depression, psychosis, ADHD, etc.), and harm reduction techniques for the use of cannabis with recommendations (these recommendations favor oral intake and are based on the recommendations for medical cannabis use
[29,30]) will be provided in an appendix accessible after login, along with frequently asked questions and their corresponding answers.

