### Trial flow

Figure 
1 provides an overview of the trial flow. If a participant successfully completes the baseline assessment (t0), he or she will be introduced step-by-step into the corresponding study arm, invited to participate in part one (study arms 1 and 2), or informed that they will be provided access to the web-based self-help within approximately 12 weeks (waiting list condition). Participant in the intervention arms 1 and 2 will receive automated e-mail notifications to login and enter their cannabis consumption frequency and quantity into their consumption diary every week. Access to all modules will be unrestricted from day one. However, the participants will be encouraged to complete all key modules (modules 1–4) in order, to complete at least two further modules chosen from modules 5 to 8 and to repeat any modules they feel they need or that they perceived as helpful within the 6 weeks of duration of study arms 1 and 2.

Six weeks after the baseline assessment, participants will again be invited by e-mail to login and complete the final study assessment (t1). Participants will be invited to complete the follow up assessment (t2) by an e-mail message that will be sent 3 months after t0; this message will inform the participants that completion of the entire 3-month follow up assessment will be compensated with 40 Euro (via an online voucher or an online charitable donation).

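### The primary quantity measure has no rule for entering oral cannabis, although the self-help appendix for arms 1 and 2 favours oral intake, so a change of route may be recorded as a reduction

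*Protocol article*

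**What the plan says.** **The outcome.** Aims of the trial: "The primary outcome is the weekly quantity of cannabis consumed (measured in the number of standard joints per week", assessed at the 3-month follow up. Measurement instruments likewise speaks of the quantity of cannabis used. Neither definition is limited to one route.

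**The instrument.** Measurement instruments has participants choose a cannabis form (low-potency plant, high-potency plant or resin) and then one of five joint pictures from 1/10 g to 1/2 g. Other preparations are handled thus: "Those who smoke cannabis in different preparations (e.g., in a bong, a vaporizer, etc.) will choose the photograph" nearest to their usual amount. For departures from the usual joint, "participants will be asked to convert the quantities of the cannabis they smoke into units relative to that picture". The rule of thumb works at equal content weight: one high-potency joint counts as two low-potency joints, one resin joint as three.

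**The intervention.** Study interventions lists, among the programme's supplementary material, "harm reduction techniques for the use of cannabis with recommendations (these recommendations favor oral intake". This material "will be provided in an appendix accessible after login". The programme is "offered as a web-based self-help intervention (study arms one and two".

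**The waiting list.** Trial flow says these participants are "informed that they will be provided access to the web-based self-help within approximately 12 weeks", which is about when the primary outcome is measured.

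**The concern.** The outcome is meant to cover all cannabis consumed, but the working instructions speak of smoking, and nothing tells a participant how to enter cannabis that is eaten or drunk. In most trials this would be a small gap affecting all arms alike. Here the intervention itself carries material favouring the route that the instructions do not address, and only the active arms can see it before the endpoint.

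Any under-recording could therefore differ by arm. Randomisation does not balance an error that the intervention induces after allocation. Neither the multiple imputation nor the GEE models under Data analysis can correct it, because the affected values are recorded, not missing. Hypotheses 1 and 2 compare arms 1 and 2 with the waiting list on exactly this quantity.

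**Working it through.** **1. Outcome, instrument and exposure side by side**

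| Element | Wording in the article | Covers oral use? |
|---|---|---|
| Outcome definition | cannabis consumed or used | Yes, by meaning |
| Pictures | rolled joints, with grams shown | Not addressed |
| Other preparations | those who smoke; bong and vaporizer as examples | Not addressed |
| Conversion instruction | quantities they smoke | Not if taken literally |
| Conversion factors | potency and form at equal weight | Could be applied, but not stated |
| Appendix advice, arms 1 and 2 | favours oral intake | Yes |
| Appendix advice, arm 3 | access at about 12 weeks | Not before the endpoint |

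The gap lies between the first row and the conversion instruction.

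**2. What it does to one record.** Take a participant whose standard joint is 1/4 g of low-potency plant and who takes 1/2 g of high-potency plant orally. The existing weight and form rule would give (0.5 / 0.25) × 2 = 4 standard joints. Read literally as an instruction about smoked cannabis, the entry is 0.

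**3. The plan's own figure, as a yardstick.** The sample size section gives Cohen's f = 0.15, 89 per group, 80% power and α = 5%. A repeated-measures F-test with 2 groups and 2 time points reproduces this if the correlation is taken as 0 (my assumption; none is stated): λ = f² × N × m / (1 − ρ) = 0.0225 × 178 × 2 = 8.01, power 80.4%. The smallest total is N = 177, that is 89 per group. For two groups f = 0.15 is d = 2f = 0.30. In a comparison at a single time point, 89 per group has 80% power for d of about 0.42. The point does not rest on these figures; they only give a scale.

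**4. Illustrative size.** Let s be the share of active-arm participants who change route, h the fraction of their use that they move, u the fraction of moved use left unrecorded, and CV the SD divided by the mean of weekly joints. With switchers of average use and no switching in arm 3:

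spurious d = (s × h × u) / CV

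None of these inputs is in the article; all are assumed. With q = s × h × u, the table gives the spurious d. In brackets is the chance of a significant result favouring the intervention when there is no true effect, Φ(d × √(89/2) − 1.96), against 2.5% in that direction without bias.

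| q | CV 0.8 | CV 1.0 | CV 1.5 |
|---|---|---|---|
| 5% | 0.06 (6.1%) | 0.05 (5.2%) | 0.03 (4.1%) |
| 10% | 0.13 (13.0%) | 0.10 (9.8%) | 0.07 (6.5%) |
| 20% | 0.25 (38.5%) | 0.20 (26.6%) | 0.13 (14.2%) |
| 30% | 0.38 (70.6%) | 0.30 (51.6%) | 0.20 (26.6%) |

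For example, s = 10%, h = 50%, u = 1 gives q = 5%; s = 30%, h = 50%, u = 1 gives q = 15%, or d = 0.15 at CV 1.0. If participants do convert oral use by weight, u = 0 and the bias is nil.

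**The case against.** **No text excludes oral use.** The outcome is cannabis used or consumed, and the conversion sentence goes on to say that it applies when someone on occasion consumes in a form other than the usual joint. A reader might infer the stronger claim that the diary records only smoked or vaporised cannabis, so that a switch necessarily counts as a reduction. The article does not support that, and it is not claimed here. The clause does not close the gap either: form was defined just before as low-potency plant, high-potency plant or resin, not as route; the object of the sentence is still what they smoke; and the clause describes a one-off exception, not a lasting change.

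**The unit can already take oral use.** This is fair. The pictures show grams, and the factors work by content weight, whatever the route. It makes the fix easy, but participants are not told to apply the rule in this way.

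**Other measures would reveal a switch.** This stands in part. Use-days is worded for any route, and the Discussion says the trial will also rely on it. CUDIT and SDS are not in joints. The substance history questionnaire asks about manner of consumption at baseline, 6 weeks and 3 months, although the abstract presents that outcome as covering non-cannabis drugs. These could flag a change of route but cannot restore the missing quantity. Fewer joints with unchanged use-days is also what a genuine reduction in the amount per day looks like.

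**Exposure is slight.** The advice is one item in an appendix; no module title or listed chat topic concerns it, and the active content promotes reduction. This stands and limits the likely size.

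**An article condenses its instruments.** On-screen instructions may say more. But the article sets out the primary measure step by step and words that step for smoking, so the stated wording is at issue, not a missing detail.

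**Conclusion.** The point holds as a gap in the definition of the primary measure, not as a demonstrated bias. The measure gives no rule for a route that the programme's appendix favours, and only arms 1 and 2 see that appendix before the 3-month endpoint. If participants who change route leave oral use out or under-convert it, the error favours the intervention under Hypotheses 1 and 2. Hypothesis 3 is largely unaffected, since arms 1 and 2 have the same appendix.

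The size is unknown. If 10% of quantity moved and went wholly unrecorded, d would be 0.07 to 0.13, roughly a quarter to under a half of 0.30. That rests on assumed uptake, complete non-recording, an assumed CV of 0.8 to 1.5 and no switching on the waiting list. A reader might infer from the bottom row of the table that the whole planned effect could be an artefact. That row needs, for instance, 30% of participants to move all their use and record none of it, and nothing in the article suggests this.

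The gap should still be closed. The Discussion says this quantity measure is new to randomised trials, and the remedy is small.

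**What to change.** - Leave the harm-reduction content as it is.
- In the conversion instruction, refer to the cannabis participants use, by any route, instead of the cannabis they smoke.
- Add an entry for cannabis not smoked or vaporised, in grams of low-potency plant, high-potency plant or resin. Use it identically in all three arms at baseline, in the diary and at 3 months, including telephone follow-up.
- Convert that entry to the participant's standard joint by the existing content-weight and form rule, and include it in the primary weekly quantity.
- Report the smoked-only quantity (vaporised use included) as a sensitivity result, so that any change of route can be seen by arm.

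The cost is one extra field and one changed instruction before launch. Gram estimates for oral products will be somewhat imprecise, which adds a little noise to the primary outcome.
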